### Eligibility Criteria

After obtaining informed, written consent, the following inclusion criteria will be verified: affiliated to a social security scheme; a male adult; a member of a combat unit with external operations (OPEX) capability; a soldier with a current contract with the Brigade, lasting a minimum of 12 months; a soldier who is able to attend all measurement sessions and workshops, according to the schedule defined upstream; a soldier who is not a member of the *Groupements Commando Montagne* (to ensure homogeneity); and, finally, nonparticipation in one of the studies included in phase 1 of the PREPAR project. The latter social psychology study aimed to understand the day-to-day experience of frontline professionals and was approved by the ethics committee of the University of Aix-Marseille (2019-12-12-001). Noninclusion criteria are as follows: being female; receiving treatment for a chronic disorder (daily medication for at least 1 month); participation in an external operation planned within 12 months; and being an adult ward of court.

### Participant Timeline

Figure 1 presents the timeline for participants, and Table 1 presents a synopsis of how the study will unfold.

**Figure 1 figure1:**
[figure not shown]
Study timeline. *: 2 to 3 hours to take measurement; △: “debriefing and anchoring of the practice” workshop.

**Table 1 table1:** Summary of the stages of the study.

	Visit 1 inclusion	+4 months	+6 months	+12 months
Information – consent	✓			
Sociodemographic data	✓			
Self-administered questionnaires	✓	✓	✓	✓
Blood and saliva collection (physio-biology and genetic)	✓	✓		✓
Emotional reactivity	✓	✓		✓
“Debriefing and anchoring of the practice” workshop			✓	✓

The first step is a briefing session with 2 of the Brigade’s companies. Each individual will receive 2 information letters (1 regarding participation in this study, and 1 regarding participation in genetic studies), in order to allow time to reflect before the inclusion visit.

### Visit 1: Inclusion

Inclusion will take place over a 3-week period. This time is needed to be able to disseminate information to the groups concerned and collect data. Once informed consent has been obtained, and eligibility criteria have been verified by one of the investigators, the following samples will be collected: (1) a 30-mL blood sample; (2) three 5-mL saliva samples (the participant will be asked to collect a sample on waking, getting up, and 30 minutes later [28]); (3) noninvasive measurements of cardiac variability and electrodermal conductance (using patches applied to the skin) during Stroop tasks, estimated to take 20 minutes; and (4) a psycho-cognitive evaluation (standardized and validated questionnaires). The latter will make it possible to evaluate the psychological and somatic symptoms (Patient Health Questionnaire [PHQ-15] [29]; psychosocial factors; Perceived Stress Scale [PSS] [30]; coping flexibility [20]; inner correspondence and peaceful harmony [ICPH] [31]; stigma and barriers to care [32]; Multidimensional Scale of Perceived Social Support [MSPSS] [33]; the Siebold vertical and horizontal cohesion questionnaire [34]; and the presence of any psychopathologies such as anxiety and depression: Hospital Anxiety and Depression Scale [HADS] [35,36], Posttraumatic Checklist-5 [PCL-5] [37], unsure, and Burnout Measure Short Version [BMS] [38,39]). The time required to fill out the questionnaires is estimated to be 45-60 minutes (184 items in total).

### The Prevention Program: Workshops

Members of the intervention group will participate in 8 workshops. Each lasts 2 hours and is divided into three parts: (1) welcome participants with time allocated for inclusion (time approximately 20 minutes); (2) a presentation of the pedagogical objectives of the session, and its practical application; and (3) group wind-up (approximately 20 minutes). Please see Multimedia Appendix 1 for a description of the workshop program. At the end of the study, members of the nonintervention group, who wish to do so, will be able to benefit from the same prevention program during a later session, which will be scheduled as a function of operational constraints.

### Visit +4 Months: Follow-up

A second round of data collection will take place at the end of the prevention program (approximately 4 months after inclusion). Each participant will be asked to allocate half a day to the collection of biopsychological measurements.

### Visit +6 Months: Follow-up

Two months after the end of the program, during the first debriefing workshop, participants will be asked to complete a set of self-administered questionnaires (the same set as the one completed during the inclusion visit a part for the sociodemographic information).

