**Methods:**

This is a single-center, prospective, randomized, parallel-group controlled cohort study. The cohort is divided into 2 groups: the nonintervention group receives no training, and the intervention group follows a dedicated prevention program (structured into 8 workshops and 2 debriefing and practice reinforcement workshops). Each participant is evaluated 4 times (at inclusion, +4 months, +6 months, and +12 months). During each visit, participants complete several psychosocial questionnaires (which take 15-80 minutes to complete). Samples (a 30-mL blood sample and three 5-mL saliva samples) are collected on 3 occasions: at inclusion, +4 months, and +12 months. Emotional reactivity (electrocardiogram and electrodermal activity) is measured before, during, and after the classic and the emotional Stroop task.

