### Objectives of the Research

The main objective is to determine the effectiveness of a biopsychosocial program targeting the resilience (developing stable resources to adapt to occupational demands, in order to cope with TEs) of military personnel in the context of PTSD prevention.

The secondary objective is to better understand interindividual variability regarding the program’s impact. We will study levels of vulnerability at inclusion and their impact on the program’s effectiveness. We will also track postprogram changes in resilience (at 6 and 12 months). In addition, we will evaluate (1) the impact of the program on activation and psychobiological deterioration biomarkers and (2) the psychosocial determinants at 4 months (the end of the program) and 12 months (to evaluate persistence). In addition, we will measure adherence to the intervention at group and individual levels, through an evaluation at the end of the program. Finally, we will examine user satisfaction with the URGOfeel sensor and its application during workshops.

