### Visit +12 Months: End of Study

Eight months after the end of the prevention program, each participant will take part in a final measurement session (lasting 2-3 hours). They will also be asked to allocate another half a day to the collection of biopsychological measurements.

Measurements recorded at +4 and +12 months are identical to those performed at inclusion, except for sociodemographic data, and the sample needed to assess vulnerability (genetic polymorphism).

Thus, all participants are required to attend 4 measurement sessions: visit 1, inclusion; +4 months; +6 months; and +12 months. During each of these visits, they will be asked to complete a self-administered (using a tablet) questionnaire to collect psychosocial data. In addition, at inclusion, +4 months, and +12 months, (1) biological samples will be collected for each participant (blood and saliva) and (2) activation of the autonomic nervous system (heart rate variability and electrodermal activity) will be measured at rest, during emotional activation (the classic, then the emotional Stroop task), and at recovery.

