#### Objective 2.5: Describe Changes in Adherence to the Intervention

Adherence will be assessed using quantitative criteria at 4, 6, and 12 months (the Treatment Motivation Questionnaire). This analysis will be based on (1) an analysis of the processes put in place to operationalize the intervention; (2) a focus group consisting of 8 participants, and 10 individual interviews carried out at 4 and 12 months after inclusion; and (3) a qualitative analysis of discussions that took place during workshops to anchor the practice held at 6 months and 1 year. The latter will also make it possible to identify both obstacles and drivers of adherence.

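### The 6-month questionnaires are completed inside a workshop that only the intervention arm has, so the 6-month contrast mixes postprogram effect with the immediate effect of the session

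*Protocol article*

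**What the plan says.** All references are to the protocol article.

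- **Setting at 6 months.** Visit +6 Months: Follow-up says that "during the first debriefing workshop, participants will be asked to complete a set of self-administered questionnaires". No arm is named.
- **Who has the workshops.** The abstract's Methods describe the intervention group's program as "structured into 8 workshops and 2 debriefing and practice reinforcement workshops" and say that "the nonintervention group receives no training". The section on the workshops adds: "At the end of the study, members of the nonintervention group, who wish to do so, will be able to benefit" from the program. Controls thus have access only once follow-up is over.
- **Who must answer.** Visit +12 Months: End of Study says that "all participants are required to attend 4 measurement sessions", and lists +6 months among them.
- **What happens at 12 months.** Table 1 ticks a debriefing workshop at both +6 and +12 months. Objective 2.5 refers to "discussions that took place during workshops to anchor the practice held at 6 months and 1 year". The +12-month visit text, however, describes a final measurement session of 2 to 3 hours and a further half day for biopsychological measurements. It does not place the questionnaires inside a workshop.
- **How the scores are used.** Objectives of the Research treats 6 and 12 months as postprogram follow-up of resilience. Objective 2.2 names PANAS, the Self-Compassion Scale and DRS-15 at those times. Statistical Methods compares the arms by repeated measures ANOVA.

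**The concern.** A between-arm comparison of self-reported scores is informative about an intervention when the two arms are measured alike. Here the intervention arm is to answer during a practice-reinforcement session, and the control arm has no such session. Any momentary effect of that session on the answers is then part of the observed arm difference at 6 months.

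What is at stake is the reading of Objective 2.2 at 6 months. The plan intends those scores to show what has become of resilience two months after the program ended. Answers given during a reinforcement session cannot show what remains without it. Setting and arm coincide completely at this visit, so no later adjustment can separate them. Only the conduct of the visit can.

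**Working it through.** **Step 1: does measurement setting coincide with arm at 6 months?**

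| Element | Intervention arm | Control arm | Source |
|---|---|---|---|
| Questionnaires required at +6 months | Yes | Yes | Visit +12 Months text; Table 1 |
| Debriefing workshop at +6 months | Yes | No: no training until the study ends | Abstract, Methods; The Prevention Program: Workshops |
| Stated setting of the questionnaires | During that workshop | Not described | Visit +6 Months |

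The stated setting can apply to one arm only, so at 6 months the setting coincides with the arm.

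**Step 2: which outcomes are exposed?** Objective 2.2 follows three scales at 6 months. The Primary End Point section describes PANAS as measuring the intensity of emotional states, self-compassion as a general tendency, and hardiness as quasi-dispositional. By the plan's own account, PANAS is the scale most open to a momentary influence, and the other two less so.

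**Step 3: can the analysis remove it?** A repeated measures ANOVA estimates the arm difference at each visit. Write the expected 6-month difference as D = L + S, where L is the postprogram effect and S the effect of answering in the session. Only D is observed. Every intervention answer contains S and no control answer does, so L and S are not separately identifiable.

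**Step 4: which other visits are affected?** At 4 months, when the primary composite is evaluated, Table 1 shows no debriefing workshop, so the primary end point is untouched. At 12 months the workshop and the measurements share a visit column, but the visit text describes a separate measurement session and gives no order. Overlap is possible, not established.

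**Step 5: how large could it be?** The documents give no value for S. The following is an illustration with an assumed S, not an estimate.

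- Assumptions: L = 0; one unadjusted two-sided 5% comparison of means; independent participants; normal approximation.
- Participants per arm: 58 planned (Sample Size); after 20% dropout, 58 × 0.80 = 46.4, taken as 46.
- With S in SD units, the noncentrality is k = S × √(n/2), and the rejection rate is P(Z > 1.96 − k) + P(Z < −1.96 − k).

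| Assumed S | n = 46: k | Rejection rate | n = 58: k | Rejection rate |
|---|---|---|---|---|
| 0.1 SD | 0.48 | 8% | 0.54 | 8% |
| 0.2 SD | 0.96 | 16% | 1.08 | 19% |
| 0.3 SD | 1.44 | 30% | 1.62 | 37% |

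With S = 0 the rate is 5%. The formula is symmetric: a negative S of the same size gives the same rate in the opposite direction.

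**The case against.** **The workshops are part of the program.** The arm contrast therefore remains a valid comparison of the whole package, debriefing sessions included. This stands. It does not support the postprogram reading that the objectives give to the 6-month scores.

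**Order within a visit is operational detail.** A condensed article may leave it to the full protocol or the workshop schedule, and the wording allows the questionnaires to come at the start of the session. This is fair as far as it goes. But the article does not merely omit the setting. It states one, and the stated setting cannot apply to controls.

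**The control setting is unknown.** This stands. Controls may also be assembled in groups, so the presence of peers is not shown to differ between arms. What differs on the text is the workshop itself.

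**Stronger readings that a reader might infer.**

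- *The 12-month persistence comparison is equally compromised.* The documents do not support this. Only Table 1 and Objective 2.5 suggest an overlap, and the visit text describes a separate measurement session. The word persistence is attached to 12 months and to the biomarker and psychosocial outcomes.
- *The bias must favor the program.* This is not shown. The program seeks to normalize talk about injury, so the setting might increase disclosure of difficulties and work against the program on some scales.
- *The effect can be expressed as a share of the 25-point difference in composite response (55% versus 30%) used for sample size.* It cannot. That composite is evaluated at 4 months, while Objective 2.2 follows changes in scores.

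**Conclusion.** The point holds for one secondary comparison: the 6-month between-arm contrast of PANAS, Self-Compassion Scale and DRS-15. As planned, that contrast combines any postprogram effect with the immediate effect of answering within a group session, most plausibly for PANAS. The conclusion rests on the stated 6-month setting, on the workshops belonging to the intervention arm alone, and on both arms answering at that visit.

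Size and direction are unknown. The rejection rates of 8% to 37% depend wholly on the assumed shifts of 0.1 to 0.3 SD and show only that a modest momentary effect would matter at this sample size. At 12 months the issue is a possible overlap that the text should rule out. The 4-month primary end point is unaffected. The change is worth making because it is cheap and analysis cannot replace it, but the trial's main conclusion does not depend on it.

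**What to change.** 1. Amend Visit +6 Months: Follow-up so that the questionnaires are completed before any workshop content, with the same setting and instructions in both arms, and describe the controls' 6-month session. No physiological measures are taken at this visit, so only the questionnaires are concerned.
2. Add to Visit +12 Months: End of Study that the questionnaires and physiological measures precede the second debriefing workshop.
3. If the 6-month data have already been collected, report the actual order and setting by arm, and describe that contrast as measured during the workshop rather than as a postprogram effect.

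The cost is a small scheduling effort within existing visits. No visit, sample or participant is added.

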### Visit +12 Months: End of Study

Eight months after the end of the prevention program, each participant will take part in a final measurement session (lasting 2-3 hours). They will also be asked to allocate another half a day to the collection of biopsychological measurements.

Measurements recorded at +4 and +12 months are identical to those performed at inclusion, except for sociodemographic data, and the sample needed to assess vulnerability (genetic polymorphism).

Thus, all participants are required to attend 4 measurement sessions: visit 1, inclusion; +4 months; +6 months; and +12 months. During each of these visits, they will be asked to complete a self-administered (using a tablet) questionnaire to collect psychosocial data. In addition, at inclusion, +4 months, and +12 months, (1) biological samples will be collected for each participant (blood and saliva) and (2) activation of the autonomic nervous system (heart rate variability and electrodermal activity) will be measured at rest, during emotional activation (the classic, then the emotional Stroop task), and at recovery.

### Outcomes

#### Primary End Point

There is no consensus in the literature regarding the definition of resilience, and there are references to several dimensions. Consequently, measuring the effect of the intervention on resilience requires the use of several indicators. A simple approach would be to measure PTSD symptomatology reported by participants, with the expectation that the intervention will result in a decrease in symptoms. Although this approach would be relevant for long-term measures [40], using this criterion in a short-term study, such as ours, would be restrictive and fail to support the processes that are assumed to be activated during the intervention [41]. The latter consists, in part, of removing barriers to seeking care when necessary, in order to support the building of resilience as a process, and not simply as a state. Our short-term approach is also justified by the difficulty of conducting studies in a military environment over the long term (personnel are transferred every 3 years) and attrition among professional soldiers.

The proposed composite criterion groups indicators of resilience that are described as protective factors for PTSD and are recognized to be sensitive to interventions. The first is the participant’s emotional state. It is known to be highly impacted in PTSD, where there is an increase in negative emotions. At the same time, it is a marker of resilience in cases where emotions become positive following trauma. We will therefore use the Positive and Negative Affect Scale (PANAS) score [42], which measures the intensity of positive and negative emotional states. Our second indicator measures self-compassion, which refers to a general tendency to be kind to oneself, despite knowing one’s failures and successes. Self-compassion is very directly linked to the process of self-acceptance and is a predictive criterion for both the development of PTSD (when it is deficient), and increased resilience (when stimulated by a psychotherapeutic intervention). Self-compassion also contributes to cognitive flexibility. Finally, the third indicator is the hardiness score. This measure is classically used in the literature to study, from a psychological point of view, an individual’s ability to remain in good health under stressful conditions. It should be noted that this measure should not, by itself, be considered a sufficient criterion for resilience in our protocol, given that any modification is observed over the long term, based on a quasi-dispositional approach.

Consequently, the hardiness score will be combined with mood and self-compassion criteria. The composite criterion will be evaluated at 4 months (Figure 1). A change in resilience will be defined as favorable if at least two of the following three criteria are met: (1) a 20% improvement in the PANAS score; (2) given the military context, and the nonspecific nature of our intervention, a 20% improvement in scores on the Self-Compassion Scale; or (3) a 5% change in hardiness, measured using the Dispositional Resilience Scale (DRS-15) [43]. If these criteria are not met, any change will be considered to be unfavorable. The choice of thresholds for variables making up the composite criterion is based on data from research conducted by the project’s teams.

#### Emotional State

The data based on the STEP study, carried out in the framework of [name]’s thesis [24], show a 33.68% long-term increase in the PANAS score among members of the *Bataillon de Chasseurs Alpins* who had undergone training (pretraining score=12.32, posttraining score=15.21, and 6-month posttraining score=16.47). Thus, in the PREPAR study, we consider a 20% improvement as significant (for questionnaire details, see Multimedia Appendix 2 [42-44]).

#### Self-Compassion

According to Kotsou and Leys [44], the mean score is 2.88 in the French population. A score between 3.5 and 5.0 indicates a high level. Thus, in the context of this study, an increase of 20% (0.62) will be considered relevant (for questionnaire details see Multimedia Appendix 2).

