#### Hardiness, the Ability to Stay Healthy Under Stressful Conditions

In the literature, global hardiness scores (measured by the DRS-15 scale) in military populations are around 29 (scores can range from 0 to 45). To the best of our knowledge, there are no studies that have evaluated the effect of a prevention program on this variable. Thus, as this is a dispositional measure, we consider a 5% increase as relevant (for questionnaire details see Multimedia Appendix 2).

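### Two responder thresholds of the primary composite are stated inconsistently: 20% of the self-compassion mean is about 0.58, not 0.62, and the hardiness criterion lacks a direction in the composite definition

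*Protocol article*

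**What the plan says.** All references are to the Outcomes part of the Methods in the Protocol article.

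- **Primary End Point** (the composite definition). A change is favorable when two or more of three criteria are met at 4 months. The self-compassion item is "a 20% improvement in scores on the Self-Compassion Scale", with no absolute number of points. The hardiness item is "a 5% change in hardiness, measured using the Dispositional Resilience Scale (DRS-15"). The PANAS and self-compassion items both ask for an improvement; the hardiness item does not.
- **Self-Compassion** (rationale for that threshold). The section reports that "the mean score is 2.88 in the French population" and that "A score between 3.5 and 5.0 indicates a high level". It then concludes "Thus, in the context of this study, an increase of 20% (0.62) will be considered relevant".
- **Hardiness** (rationale for that threshold). Global scores "in military populations are around 29 (scores can range from 0 to 45"), and "as this is a dispositional measure, we consider a 5% increase as relevant".

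Under Statistical Methods, the primary analysis compares the percentage of responders between groups with a chi-squared test.

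**The concern.** The endpoint is a yes/no classification, so the thresholds are the endpoint. Each should be one rule that two people would apply in the same way.

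For self-compassion, a percentage and a number of points are printed as equivalent, and they are not, even at the mean given two sentences earlier. Applied to individuals, a percentage of the soldier's own baseline and a fixed number of points are different kinds of rule, and they diverge further away from the mean.

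For hardiness, the definition that an analyst would program names no direction, while the section that justifies it does.

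If either ambiguity is still open when outcome data are available, the choice of reading could be made, or appear to have been made, with the result in view.

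**Working it through.** **Inputs** (Protocol article): self-compassion mean 2.88, high level from 3.5, threshold 20% and 0.62 (Self-Compassion); hardiness about 29 on a 0 to 45 scale, threshold 5% (Hardiness); 58 per group, 20% dropout, response rates 55% and 30% (Sample Size).

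**Step 1. Try to reproduce 0.62.**
- 20% of the cited mean: 0.20 × 2.88 = 0.576, about 0.58.
- 20% of the high-level cut-off: 0.20 × 3.5 = 0.70.
- Cut-off minus mean: 3.5 − 2.88 = 0.62. Only this gives the printed figure.
- As a percentage of the mean: 0.62 / 2.88 = 21.5%.
- Base needed for 0.62 to be 20%: 0.62 / 0.20 = 3.10, which the article does not give.

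As a comparison, the PANAS percentage in the Emotional State section does reproduce: (16.47 − 12.32) / 12.32 = 33.685%, printed as 33.68%. The self-compassion figure does not.

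**Step 2. Does the difference matter for a soldier?** Assume that 20% is taken from the soldier's own baseline and that 0.62 is used as a fixed cut-off.

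| Baseline | 20% of baseline | 0.62 as % of baseline |
|---|---|---|
| 2.0 | 0.40 | 31.0% |
| 2.88 | 0.576 | 21.5% |
| 3.10 | 0.62 | 20.0% |
| 3.5 | 0.70 | 17.7% |
| 4.0 | 0.80 | 15.5% |

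The two rules coincide only at a baseline of 3.10. They can disagree in either direction:
- 2.88 to 3.48: +0.60, 0.60 / 2.88 = +20.8%. Meets 20%, fails 0.62.
- 3.50 to 4.15: +0.65, 0.65 / 3.50 = +18.6%. Fails 20%, meets 0.62.

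**Step 3. Hardiness.** 5% of 29 is 1.45 points. A fall from 29 to 27 is −2 / 29 = −6.9%. It is a change of more than 5%, so it meets the bare wording of the composite definition. It is not an increase, so it fails the Hardiness section.

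**Step 4. How few reclassified soldiers would matter?** With 20% dropout, 58 × 0.80 = 46.4, so about 46 per group. The planned rates give 0.55 × 46 = 25.3 and 0.30 × 46 = 13.8, so 25 and 14 responders.

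| Responders of 46, intervention vs nonintervention | p, uncorrected chi-squared | p, continuity-corrected |
|---|---|---|
| 25 vs 14 | 0.020 | 0.035 |
| 24 vs 14 | 0.034 | 0.057 |
| 23 vs 14 | 0.056 | 0.089 |

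This illustrates sensitivity only. It does not predict how many soldiers would be reclassified, or in which group.

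**The case against.** **Hardiness.** A reader might infer that the plan counts a 5% fall in hardiness as a success. The documents do not support that. The item belongs to a definition of a favorable change in resilience, hardiness is presented there as a protective indicator, and the section that justifies the threshold asks for an increase. Read together, only one direction is possible. What stands is that the composite definition omits a word that the other two items and the hardiness section supply.

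**Self-compassion.** A reader might also infer that the plan has two competing operative rules. The composite definition contains only the 20% rule; 0.62 is a parenthesis in the rationale. Misclassification arises only if someone uses 0.62 as the cut-off, and at the cited mean the gap is just 0.62 − 0.576 = 0.044 points. This is fair, and it limits the consequence. It does not remove the error: the rationale equates two unequal quantities, and the composite definition does not say what the 20% is a percentage of.

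**Bias.** Either reading would apply to both groups alike, and the sample size uses assumed response rates rather than these thresholds. Both points stand: no bias between groups is shown and the planned numbers are untouched.

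**Documents not shown.** Questionnaire details are referred to Multimedia Appendix 2, and the full protocol is not available here. Either may hold a clean statement of the rules. The article's own figures and wording would still need to be reconciled with it.

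**Conclusion.** The concern holds as an inconsistency in how two primary-endpoint thresholds are written.

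- **Self-compassion.** The printed equivalence is wrong. 20% of 2.88 is 0.576; 0.62 is 21.5% of 2.88 and equals the gap to the high-level cut-off. That this gap is where 0.62 came from is an inference from the exact match; the article does not say so. Soldiers would be classified differently only if 0.62 were applied instead of 20%. The size of the discrepancy at baselines other than the mean rests on the assumption that the percentage is taken from each soldier's own baseline.
- **Hardiness.** The composite definition conflicts in wording with the hardiness section, but the intended direction is recoverable.

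How much the trial's response rates would shift cannot be stated, because the article gives no score variances or correlations. No estimate is offered. The point merits correction because, at about 46 analysed soldiers per group, reclassifying one or two can move the primary p-value across 0.05, and because the correction costs almost nothing.

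**What to change.** Before outcome data are analysed, state one base, one value and one direction for each scale, and use the same statement in the Primary End Point section and in the section for that scale.

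- **Hardiness.** In the composite definition, replace the 5% change by an increase of at least 5%.
- **Self-compassion.** Keep the 20% rule of the composite definition and say that it is relative to each soldier's own baseline. In the Self-Compassion section, delete the 0.62 or correct it to about 0.58 at the mean of 2.88, as an illustration only. If the authors instead intend an absolute rule of 0.62 points, state that alone in both sections and drop the 20%.

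Replacing the percentages by a fixed 0.58 points or 2 hardiness points would not be a neutral correction. A fixed 0.58 is 29% of a baseline of 2.0 and 14.5% of a baseline of 4.0. In whole hardiness points, 5% of own baseline is reached with 1 point at baselines up to 20 and needs 3 points above 40. Whether a threshold is relative or absolute is for the authors to decide.

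The cost is a few words of text. No data collection, sample size or analysis method changes.
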